## **5.2 Breaking the Study Blind**

This is a partially blinded randomized study, with patients and outcome assessors blinded to treatment allocation. Given the physical differences in the products and the emergency nature of the intervention, attending clinicians will not be blinded to the treatment. Thus, breaking the study blind is not an issue in this study.

The random allocation schedule will be prepared by a biostatistician not involved in the conduct of the trial (see **Section 9.3**). To minimize bias, neither the individual randomizing nor any of the health care providers will know which treatment will be assigned to a given patient when coagulation factor replacement is ordered. Blood products will be transported to the OR in weighted temper-proof boxes to maintain the blind until IMP infusion.

The type of IMP administered will not be recorded in the chart to ensure that the research personnel assessing outcomes and AEs are blinded to assignment. Patients will also be blinded to treatment allocation.

## **5.3 Treatment Compliance**

### **5.3.1 IMP Dispensing and Accountability**

IMP dispensing and accountability procedures will be as per standard practice at the participating centres.

### **5.3.2 Assessment of Treatment Compliance**

Coagulation factor replacement will be ordered and administered by the clinical team in the hospital and will not be dependent on patient compliance.

## 6 STUDY CONDUCT

All patients having cardiac surgery with or without CPB at the study centres will be the potential patients in the study. Patients will be randomized if they bleed or are thought to have a high potential to bleed (see section 4.1.1) after the start of surgery and the clinical team determines that coagulation factor replacement is required according to current clinical standards for up to 24 hours after randomization. Once the clinical team orders coagulation factor replacement, the blood bank technologist will confirm patient eligibility and randomize the patient (according to a prepared randomization schedule) to *Octaplex* or FP and prepare the product.

For 24 hours from randomization, patients may receive 1500 IU *Octaplex* for IBW $\leq$ 60 kg or 2000 IU *Octaplex* for IBW $>$ 60 kg, or 3 U FP for IBW $\leq$ 60 kg or 4 U FP for IBW $>$ 60 kg, as per randomized group allocation. If an order for a second dose is received, the second dose of *Octaplex* or FP will be released and administered to patients according to the randomized group allocation as per the first dose. For any additional doses (i.e., the third dose and thereafter), patients in both groups will receive FP (in 1 U increments at the discretion of the ordering physician).

Standard coagulation measures, including INR, EXTEM CT and MCF, and fibrinogen level, will be obtained as per usual clinical practice ideally within 75 minutes before and after each IMP administration. Due to the nature of bleeding in these cases, however, IMP doses can be administered before these results are obtained or the test results are released by the laboratory. Clinical indications for IMP administration are bleeding in the setting of suspected or confirmed low coagulation factor levels, as indicated by EXTEM CT  $>90$  seconds, which is the treatment threshold recommended by the validated and standardized TACS algorithm (see Figure 2; next page) (4), or INR  $>1.5$ . In certain circumstances, such as uncontrolled bleeding, clinicians may deem it necessary to administer coagulation factor replacement in cases where EXTEM CT is  $<90$  seconds (or INR is  $<1.5$  if ROTEM not being used).

All AEs and SAEs occurring until POD-28 will be recorded. Patients will be followed by research coordinators in each institution. All clinical outcomes will be obtained from patients' medical records and electronic records, history and physical where needed, and via phone contact during the follow-up visits.

The flow chart of assessments by study visit is given on page 9.

[figure not shown]

**Figure 2.** Cardiac Surgery Blood Transfusion Algorithm from TACS. Point-of-care (POC) tests consisted of ROTEM (Thromboelastometry; Tem International GmbH, Munich, Germany) and Plateletworks (Helena Laboratories, Beaumont, TX) systems. ROTEM measures included A10-EXTEM (clot amplitude at 10 minutes with the ROTEM extrinsic pathway assay: 90 s implies poor clot initiation possibly because of reduced coagulation factor levels or reduced thrombin generation). Functioning platelet count was obtained by the Platelet Works assay. ACT indicates activated clotting time; CPB, cardiopulmonary bypass; IBW, ideal body weight.

## 6.1 Study Procedure

### 6.1.1 Prior to Enrolment

#### **First coagulation factor replacement order from the surgical team received at the blood bank**

The blood bank technologist will confirm the following:

- Eligibility criteria are met
- Coagulation measures (coagulation profile) are available or have been collected or will be collected before the IMP is infused

#### **The blood bank technologist will then randomize patients to Octaplex or FP according to the randomization schedule, and prepare and release the product**

#### **Subsequent coagulation factor replacement orders for 24 hours from randomization**

- The MLT will ensure Coagulation measures (ROTEM or INR) are available, have been collected, or will be collected before IMP administration.
- If no, ask for sample to be sent to the laboratory prior to and after (within 75 min of) the administration of IMP

#### **Time of IMP infusion in the Operating Room (OR)**

The following information will be collected:

- Start time of IMP administration.
- Time of coagulation analyses (coagulation profile).

### 6.1.2 Visit 1: First post-randomization visit (0 to 24 hours after randomization)

For any specified activity that cannot be completed on this visit, additional visits will be made until all study data are obtained.

- Obtain consent from patient or surrogate
- Collect baseline data
  - Demographics
  - Medical history
  - Preoperative concomitant medications
- Collect surgical data
  - Intraoperative concomitant medications
  - CPB start and end times
  - Cross-clamp time
  - Circulatory arrest start and end times
  - Fluid in- and output monitoring
  - Inotropes and vasopressors
- Collect laboratory assessments where available as part of routine care
  - Chemistry (sodium, potassium, chloride, bicarbonate, pH)

- Hematology (complete blood count)
  - Coagulation profile before and after IMP administration
  - Safety labs (creatinine, liver function tests [ALT, ALP], bilirubin, troponin)
- Collect all transfusion and hemostatic agents (number and timing) for the 24 hour period after randomization
- Collect bleeding components using the e-CABG and UDPB criteria (1, 72) as well as a modified version of the UDPB not including PCC and FP requirements
- Collect extubation time
- Collect concomitant medications
- Collect AEs and SAEs

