##### 3.1.1 Efficacy Endpoints

###### *Primary Endpoints:*

1. Treatment response, defined as effective if no additional hemostatic intervention (such as administration of hemostatic agents including a second dose of IMP, platelet transfusion, or surgical re-exploration) from 60 minutes to 4 and 24 hours after initiation of the first dose of IMP (otherwise will be defined as not effective). If the dose of IMP is repeated within less than 60 minutes, treatment response to the IMP will be assessed for the 60 minutes after the second IMP dose only.
2. Amount of allogeneic blood products (for each type of product and cumulatively) administered during the first 24 hours after the start of surgery.
3. Number of patients who do not receive any RBC transfusions or any allogeneic blood transfusions during the first 24 hours after the start of surgery.

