###### *Exploratory Endpoints:*

1. Number of partial or full IMP doses of PCC and FP administered during the first 24 hours after the start of surgery.
2. Incidence of major bleeding, using the validated e-CABG and universal definition of perioperative bleeding (UDPB) in cardiac surgery (1, 72) scores and their individual components during the first 24 hours after start of surgery, as well as a modified version of the UDPB not including PCC and FP requirements.
3. Amount of allogeneic blood products (for each type of product and cumulatively) from start of surgery to postoperative day (POD)-7.
4. Number of patients who do not receive any RBC transfusions or any allogeneic blood transfusions from start of surgery to POD-7.
5. Number of patients receiving recombinant activated factor VII (rFVIIa) during the first 24 hours after the start of surgery
6. Number of patients receiving fibrinogen concentrate during the first 24 hours after the start of surgery.
7. Change in coagulation parameters (INR, ROTEM [EXTEM CT and MCF] and fibrinogen levels) within 75 minutes before and after IMP administration, where performed as part of standard of care.
8. Time elapsed from first IMP administration to time leaving the operating room.

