### 6.1.3 Visit 2: Postoperative days 2-7 (or at discharge if earlier)

- Collect daily laboratory assessments where available as part of routine care
  - Chemistry (sodium, potassium, chloride, bicarbonate, pH)
  - Hematology (complete blood count)
  - Coagulation profile
  - Safety labs (creatinine, liver function tests [AST, ALT], bilirubin, troponin)
- Collect transfusion requirements
- Collect extubation time (if applicable)
- Collect length of stay in the ICU and hospital (if applicable)
- Collect AEs and SAEs

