#### **7.2.2 Transfusion Data**

Details of all blood products and hemostatic agents released from the blood bank and transfused will be collected from the blood bank databases. These include allogeneic blood products (RBCs, pooled or apheresis platelets, and plasma) and albumin. Other hemostatic agents include: desmopressin, fibrinogen concentrates, rFVIIa, idarucizumab, and andexanet alpha.

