- *during the first 24 hours after randomization,*
- *during the first 24 hours after the start of first IMP dose.*

as well as a modified version of the UDPB not including PCC and FP requirements.

S3. Amount of allogeneic blood products (for each type of product and cumulatively)

- from start of surgery to postoperative day 7,
- *from end of CPB to postoperative day 7,*
- *from randomization to postoperative day 7,*
- *from start of first IMP dose to postoperative day 7.*

S4. Number of patients who do not receive any allogeneic blood product (in total and for each type separately)

- from start of surgery to postoperative day 7.
- *from end of CPB to postoperative day 7,*
- *from randomization to postoperative day 7,*
- *from start of first IMP dose to postoperative day 7.*

S5. Number of patients receiving recombinant activated factor VII (rFVIIa)

- during the first 24 hours after the start of surgery
- *during the first 24 hours after the end of CPB,*
- *during the first 24 hours after randomization,*
- *during the first 24 hours after the start of first IMP dose.*

S6. Number of patients receiving fibrinogen concentrate

- during the first 24 hours after the start of surgery.
- *during the first 24 hours after the end of CPB,*
- *during the first 24 hours after randomization,*
- *during the first 24 hours after the start of first IMP dose.*

S7. Change in coagulation parameters (INR, ROTEM [EXTEM CT and MCF] and fibrinogen levels) within 75 minutes before and after IMP administration, where performed as part of standard of care.

S8. Time elapsed from first IMP administration to time leaving the operating room.

|                           |                 |             |               |
|---------------------------|-----------------|-------------|---------------|
| Statistical Analysis Plan | Version 2.0     |             | Page 14 of 19 |
| Sponsor                   | [name] | Protocol No | FARES         |

S9. Treatment response, defined as effective if no additional hemostatic intervention (such as administration of hemostatic agents including a second dose of IMP, platelet transfusion, or surgical re-exploration) in the time windows

- from 60 minutes to 4 and 24 hours after initiation of the first dose of IMP,
- *from initiation of the first dose of IMP to 4 and 24 hours.*

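### The Visit 1 transfusion line starts at randomization, but the primary transfusion endpoints start with surgery, so the dated visit schedule does not cover the endpoint windows

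*Combined protocol and SAP*

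**What the plan says.** **Collection.** Protocol 6.1.2 (Visit 1) has the line "Collect all transfusion and hemostatic agents (number and timing) for the 24 hour period after randomization". The next scheduled contact, in 6.1.3, is headed "Visit 2: Postoperative days 2-7 (or at discharge if earlier") and asks for transfusion requirements without giving a period. Table 1 ticks transfusions under a 0 to 24 h post-randomization column and a POD 2-7 column. Protocol 7.2.2 names the source: "Details of all blood products and hemostatic agents released from the blood bank and transfused will be collected from the blood bank databases". It gives no start, no end and no requirement for times.

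**Endpoints.** Protocol 3.1.1 defines the second primary endpoint as "Amount of allogeneic blood products (for each type of product and cumulatively) administered during the first 24 hours after the start of surgery" and the third as "Number of patients who do not receive any RBC transfusions or any allogeneic blood transfusions during the first 24 hours after the start of surgery". SAP 4.6 keeps these as P2 and P3 and adds further windows from end of bypass, randomization and first dose. It also starts S2 (major bleeding), S5 (rFVIIa) and S6 (fibrinogen concentrate) at the start of surgery. S3 and S4 run "from start of surgery to postoperative day 7". The 24-hour treatment response (P1) ends 24 hours after the first dose begins.

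**Order of events.** The Study Outline, under Duration of Treatment, places randomization in the operating room. Protocol 3.2 ties it to the blood bank's receipt of the first order for factor replacement.

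**The concern.** The only instruction that asks for number and timing over a stated period begins at randomization. Two of the three primary endpoints begin earlier. Transfusion before randomization is plausible: protocol 4.2.1 gives a red cell threshold for use during surgery, and one entry route in 4.1.1 requires more than 2 hours on pump.

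If the eCRF or the database extract were built from the Visit 1 line, P2 would be too low for its stated window. A patient given red cells on bypass and none afterwards would be counted in P3 as free of red cells. Protocol 1.2 says that the pilot's results will feed the Phase 3 sample size calculation and choice of primary outcome, so the level of these endpoints matters as well as the contrast between arms.

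**Working it through.** The plan states no figure on this point, so there is nothing to reproduce. The check sets the windows side by side.

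**Inputs**
- Visit 1 line: randomization to 24 h after randomization (6.1.2).
- P2 and P3: start of surgery to 24 h later (3.1.1, SAP 4.6).
- S3 and S4: start of surgery to POD-7 (3.1.1, SAP 4.6).
- Visit 2: POD 2-7 or discharge (6.1.3).
- T, hours from start of surgery to randomization: not given; assumed 2 to 8 h.
- h, clock hour of randomization: not given; examples used.
- L, hours from randomization to first infusion: not given; assumed 0.25 to 1.5 h.

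**1. Start of the P2/P3 window.** The share before randomization is T/24.

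| T (h) | Share of the 24 h |
|---|---|
| 2 | 2/24 = 8.3% |
| 3 | 3/24 = 12.5% |
| 4 | 4/24 = 16.7% |
| 6 | 6/24 = 25.0% |
| 8 | 8/24 = 33.3% |

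This is a share of hours, not of transfusions.

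**2. End of the P2/P3 window.** The Visit 1 window ends T hours after the P2/P3 window does, so nothing is missed at that end.

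**3. POD-1 in S3/S4.** If PODs are calendar days and surgery falls on day 0, the Visit 1 window closes at clock hour h on POD-1, and 24 - h hours remain before POD-2. Randomization at 10:00 leaves 14 h, at 14:00 leaves 10 h, and at 20:00 leaves 4 h. S3 and S4 also miss the same first T hours as P2 and P3.

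**4. Windows that end 24 h after the first dose.** These pass the end of the Visit 1 window by L. For P1 from 60 minutes to 24 h, a 23 h window, the share is L/23: 0.25/23 = 1.1%, 0.5/23 = 2.2%, 1/23 = 4.3%, 1.5/23 = 6.5%. The protocol's background section says that plasma needs matching and thawing, which can delay it, so L may be longer in the plasma arm.

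**5. Endpoints that are not affected.** S1 counts study doses. Randomization happens at the first order for PCC or plasma, so no study dose precedes it, and the S1 window closes before the Visit 1 window. For the same reason the study plasma and PCC in P2 lose nothing before randomization.

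**6. After alignment.** If Visit 1 runs from the start of surgery and Visit 2 collection begins where Visit 1 ends, the uncovered time for P2, P3, S3 and S4 is 0 h.

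**The case against.** The strongest reply is that the plan already provides these data. Section 7.2.2 covers all released and transfused products with no time limit. Section 4.2.1 requires all hemostatic products to be recorded. Visit 1 reaches back before randomization for bypass times, intraoperative medications and fluid balance, and its bleeding scores use transfusion counts. It also allows extra visits until the data are complete. The SAP was revised after a blinded data review and still analyses from the start of surgery, so it presupposes the earlier data. The POD-1 gap depends on reading the Visit 2 heading as a collection period. Finally, transfusions before randomization cannot be influenced by allocation.

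Much of this stands. A reader might infer that part of each endpoint window is simply not ascertained, or that P2 is biased by some stated percentage. The documents support neither. Section 7.2.2 is a usable source, and the documents give no pre-randomization transfusion rate from which to compute a bias. Nor can the any-product part of P3 be miscoded for a plasma-arm patient treated as assigned, because that patient receives plasma after randomization.

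It does not remove the contradiction. Section 7.2.2 sets no dates and does not ask for times, and a 24-hour endpoint cannot be derived without times. The extra visits complete the listed activity, and that activity is itself limited to the period after randomization. Independence from allocation protects a difference in means in expectation. It does not protect the level of P2, the transfusion-free rate in P3, or a ratio of means.

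**Conclusion.** The point holds as an inconsistency that should be corrected. Taken alone, the dated visit schedule leaves three segments uncovered:
- the time from start of surgery to randomization, for P2, P3, S2, S5 and S6 and at the start of S3 and S4: 8.3% to 33.3% of a 24-hour window under the assumed 2 to 8 h;
- the rest of POD-1 for S3 and S4, for example 4 to 14 h for randomization between 20:00 and 10:00, and only if a POD is a calendar day;
- the last L hours of the windows ending 24 h after the first dose, about 1% to 7% of the P1 window under the assumed lag.

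For blood bank products, a full extract under 7.2.2 would reduce all three to zero. The harm is therefore conditional on the eCRF or extract following the Visit 1 line literally. No sample size or power figure in the plan changes.

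**What to change.** - **6.1.2:** collect all transfusions and hemostatic agents, with number and time, from the start of surgery as used in the endpoints until the later of 24 h after randomization and 24 h after the start of the first IMP dose.
- **6.1.3 and Table 1:** collect transfusions from the end of that window through POD-7.
- **7.2.2:** state that the blood bank extract includes times and runs continuously over the same period.

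If data have already been collected, confirm and record in the study report that the extract began at the start of surgery and ran without a break to POD-7. The cost is a few lines of wording and, at most, a check of the extract's date limits, because the source already exists.

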### 6.1.3 Visit 2: Postoperative days 2-7 (or at discharge if earlier)

- Collect daily laboratory assessments where available as part of routine care
  - Chemistry (sodium, potassium, chloride, bicarbonate, pH)
  - Hematology (complete blood count)
  - Coagulation profile
  - Safety labs (creatinine, liver function tests [AST, ALT], bilirubin, troponin)
- Collect transfusion requirements
- Collect extubation time (if applicable)
- Collect length of stay in the ICU and hospital (if applicable)
- Collect AEs and SAEs

### 6.1.4 Visit 3: Postoperative day 28 (in person if in hospital or by phone)

- Collect AEs and SAEs
- Collect extubation time (if applicable)
- Collect length of stay in the ICU (if applicable)
- Collect length of stay in the hospital (if hospital stay is extended)
- Collect concomitant medications
- Document patient outcome at 28-days (still in hospital; dead or alive)

After Visit 3 or on POD-28, the clinical study is considered completed for the patient. No further study-related assessments will be performed, unless safety concerns (e.g., ongoing AEs) require follow-up.

### 6.1.5 Time Windows Used in this Study, including Tolerances

In this study, the following time windows and tolerances apply:

**Table 3 Time Windows Used in this Study**

| Time point     | Time stated               | Tolerance        |
|----------------|---------------------------|------------------|
| Blood sampling | Before IMP administration | Up to 75 minutes |
|                | After IMP administration  | Up to 75 minutes |

## 6.2 Duration of Study

### 6.2.1 Planned Duration for an Individual Patient

The **duration of the treatment period** is 24 hours from time of randomization.

The **duration of the study** for an individual patient is 28 days from patient enrolment when patients will be contacted in person or by phone post-discharge.

### 6.2.2 Planned Duration for the Study as a Whole

The study will be considered completed when 120 patients are randomized and have finalized day 28. It is estimated that the study will take approximately 9 months for recruitment.

### 6.2.3 Premature Termination of the Study

The Sponsor, in consultation with the IDSMC, reserves the right to terminate the study at any time. In this event, any necessary procedures will be arranged on an individual study basis after review and consultation by both parties. In terminating the study, the Investigators will ensure that adequate consideration is given to the protection of the patients' interests.

Regulatory authorities and research ethics boards (REBs) will be informed in accordance with national regulations.

Early termination of the study as a whole or by centre may apply for the following reasons:

#### **Early Termination of the Entire Clinical Study**

At any time, the study will be terminated prematurely if:

New toxicological or pharmacological findings or safety reports invalidate the earlier positive benefit-risk-assessment.

#### **Early Termination at an Individual Study Centre**

At any time, the study can be terminated at an individual centre if:

- The centre cannot comply with the requirements of the protocol.
- The centre cannot comply with GCP standards.
- The a priori determined required recruitment rate is not met.

